### Randomization and Blinding

Randomization will be conducted automatically when a token code is generated alongside a unique proxy identifier (managed by researcher GW). At this point, participants are automatically randomized to receive the control or intervention arm and are blinded. The randomization procedure is carried out automatically via a randomization algorithm with no human involvement except to provide a proxy identifier. As allocations are generated dynamically, it is not possible to view future allocations. Researchers DL and GW will be unblinded to treatment allocation to enable the management of the BeAlcoholSmart and DrinksRation platforms as well as participant recruitment and retention, whereas researcher EC will be unblinded to treatment allocation to prepare statistical reports. Researchers DL and EC will not be involved in any participant engagement or recruitment. All other members of the study team will be blinded to treatment allocation.

### Messaging: Push Notifications and Email Messaging

Participants in the intervention arm (DrinksRation) will receive personalized push notifications to prompt them to use the drinks diary, engage with the app, and complete outcome measures, as well as to suggest alternative behaviors, provide feedback on goals, and promote a healthy lifestyle. We will use a bank of 180 messages developed previously [13], informed by the Health Action Process Approach framework and targeting specific BCTs.

DrinksRation uses baseline and weekly questionnaires to inform participant messaging and provide an individualized participant-centric approach. Baseline measurements are used to identify suitable messages, and as a participant engages with DrinksRation, regular measurements, including questionnaires (baseline and weekly questionnaires) and the drinks diary, are used to reflect current behavior and attitude. The notifications cover a wide range of topics to target beliefs and motivations with the primary aim of increasing the participant’s awareness of their drinking habits and behaviors. The notifications are divided into 3 categories: tailored (personalized to drinking habits as well as baseline and weekly questionnaires), tailored and triggered (tailored to baseline and contiguous measurements and a specific event occurring), and targeted (generic; sent on specific days to highlight inactivity, to remind participants to complete a questionnaire, or to alert participants to a new feature).

The system automatically decides when a message should be sent.

For the control arm (BeAlcoholSmart), participants will only receive notifications (via email) when they join the platform and when outcome measures are due. The welcome email will contain information on how to use the BeAlcoholSmart platform and when future notifications will be sent. The questionnaire emails will include a reminder to consult the BeAlcoholSmart platform and complete a questionnaire. No other notifications will be sent.

### Study Instruments

#### Overview

A summary of measures and data collection time points in this study is presented in Table 1.

**Table 1 table1:** Summary of measures and data collection time points (days 0, 7, 14, 21, 28, 56 and 84).

Measure (Multimedia Appendix 3)			Days after randomization																																
			0					7					14					21					28					56					84 (primary end point)		
			I^a^		C^b^		I			C		I			C		I			C		I			C		I			C		I			C
**Questionnaires**																																			
	Informed consent or consents	✓		✓																															
	Sociodemographics	✓		✓																															
	Depression (PHQ-2^c^) [31]	✓		✓		✓					✓					✓					✓					✓			✓		✓			✓	
	Anxiety (GAD-2^d^) [32]	✓		✓		✓					✓					✓					✓					✓			✓		✓			✓	
	ITQ-PTSD^e^ [33]	✓		✓																	✓			✓		✓			✓		✓			✓	
	Readiness-to-Change Ruler [34]	✓		✓																	✓			✓		✓			✓		✓			✓	
	Self-Efficacy Ruler [34]	✓		✓																	✓			✓		✓			✓		✓				
	AUDIT^f^ [35]	✓		✓																	✓			✓		✓			✓		✓				
	EQ-5D-5L [36]	✓		✓																	✓			✓		✓			✓		✓			✓	
	7-d TLFB^g^ for alcohol consumption [24]	✓		✓																	✓			✓		✓			✓		✓			✓	
	Adverse event reporting																				✓			✓		✓			✓		✓			✓	
	Usability evaluation																																		
	Qualitative interviews^h^																														✓			✓	
	MAUQ^i^ [37]																				✓			✓		✓			✓		✓			✓	
**Remote data collection (continuous)**																																			
	Wearable sensors^j^	✓		✓		✓			✓		✓			✓		✓			✓		✓			✓		✓			✓		✓			✓	
	Smartphone sensors^j^	✓		✓		✓			✓		✓			✓		✓			✓		✓			✓		✓			✓		✓			✓	

^a^I: intervention arm data collected via app.

^b^C: control arm data collected via Qualtrics (Qualtrics International Inc) through BeAlcoholSmart platform.

^c^PHQ-2: Patient Health Questionnaire-2.

^d^GAD-2: Generalized Anxiety Disorder-2.

^e^ITQ-PTSD: International Trauma Questionnaire for Posttraumatic Stress Disorder.

^f^AUDIT: Alcohol Use Disorders Identification Test.

^g^TLFB: Timeline Follow Back.

^h^A total of 10 participants will be invited to participate in a qualitative interview after day 84.

^i^MAUQ: mHealth App Usability Questionnaire.

^j^Additional participant consent is required.

#### Baseline Measures

After they have downloaded the respective platforms, participants will be asked to complete a baseline questionnaire to assess physical and mental health, readiness to change, self-efficacy, health status, and sociodemographics (eg, age, gender, ethnicity, employment status, and occupation). The questionnaire set is available in Multimedia Appendix 3, and the schedule is presented in Table 1.

#### Outcome Measures

The primary outcome in this study is self-reported alcohol consumption measured by the 7-day Timeline Follow Back for alcohol consumption. At baseline (day 0) and 28, 56, and 84 days after randomization, participants will be asked to report the number and types of drinks that they consumed in each of the previous 7 days via DrinksRation or BeAlcoholSmart. Using standard unit measurements (Multimedia Appendix 4), we will calculate weekly alcohol consumption for baseline and each follow-up by summing the number of units assigned to each drink. To maximize the completion of the primary outcome at each follow-up, participants will first be asked to complete the primary outcome measure before completing the rest of the questionnaire. The secondary outcome is the change in the Alcohol Use Disorders Identification Test score, measured at baseline (day 0) and day 84 follow-up between the control and intervention groups.

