**Methods:**

In this 2-arm single-blinded RCT, a smartphone app that includes interactive user-focused features tailored toward the needs of female veterans and designed to enhance participants’ motivations to reduce the amount of alcohol they consume is compared with the UK Chief Medical Officer guidance on alcohol consumption. The trial will be conducted among women who have served at least 1 day of paid service in the UKAF. Recruitment, consent, and data collection will be carried out automatically through the DrinksRation app or the BeAlcoholSmart platform. The primary outcome is change in self-reported weekly alcohol consumption between baseline (day 0) and the 3-month follow-up (day 84) measured using the Timeline Follow Back for alcohol consumption. The secondary outcome is the change in the Alcohol Use Disorders Identification Test score measured at baseline and 3-month follow-up between the control and intervention groups. The process evaluation measures include (1) app use and (2) usability ratings as measured by the mHealth App Usability Questionnaire.

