#### Control Arm

The control arm will receive access to the BeAlcoholSmart PWA. A PWA is a website that looks and behaves like a smartphone app. The PWA can take advantage of smartphone features such as push notifications and haptics without requiring the participant to download it via an app store. The BeAlcoholSmart PWA will be accessible to participants in the control arm via a unique link. The app will contain a 7-day alcohol unit calculator and generic public health guidance on safe drinking [20]. Participants will also receive reminders via email prompting them to consult the guidance provided as part of the BeAlcoholSmart PWA. Control participants will be invited to complete all questionnaires via Qualtrics (Qualtrics International Inc), with an email reminder being sent when they are due.

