### Sample Size Calculation

A power calculation was performed based on previously reported data from the DrinksRation RCT [12]. With 148 participants (n=74, 50% per arm), we will have at least 80% power to detect a difference in alcohol consumption of 3 units (approximately 30 g of alcohol/wk) between the intervention and control arms at the 84-day follow-up assessment. This calculation assumes an SD of 5.6 units, an attrition rate of 40% by day 84, a correlation between successive follow-up assessments of 0.7, and an α of 5%.

We have chosen a minimum difference of 3 units based on treatment effects observed in similar studies [26-28] and in reductions observed in the DrinksRation feasibility trial [11] and the confirmatory RCT among help-seeking veterans [12], which found reductions at 28 days of 22 units between the arms. We have chosen a smaller minimum difference of 3 units, recognizing that treatment effects for brief interventions reduce over time and that the target population for this study is not a help-seeking population.

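### Table 1 schedules no control-arm AUDIT at day 84, contradicting the definition of the only secondary outcome

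*Protocol article*

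**What the plan says.** All references are to the protocol article.

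- **Outcome definition.** Outcome Measures: "The secondary outcome is the change in the Alcohol Use Disorders Identification Test score, measured at baseline (day 0) and day 84 follow-up between" (both arms are then named). The Methods paragraph of the Abstract has the same definition: "measured at baseline and 3-month follow-up between the control and intervention groups". AUDIT is the only secondary outcome that either place names.
- **Schedule.** Baseline Measures makes Table 1 the schedule: "The questionnaire set is available in Multimedia Appendix 3, and the schedule is presented in Table 1". In Table 1 the AUDIT row is ticked for both arms at days 0, 28 and 56. At day 84 only the intervention column is ticked.
- **Meaning of the blank column.** The table footnote reads: "C: control arm data collected via Qualtrics (Qualtrics International Inc) through BeAlcoholSmart platform".
- **Control-arm collection.** The Control Arm section says: "Control participants will be invited to complete all questionnaires via Qualtrics (Qualtrics International Inc), with an email reminder being sent when they are due". It ties no instrument to a day.

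**The concern.** The secondary outcome compares two changes, so it needs AUDIT in each arm at day 0 and at day 84. The printed schedule supplies three of those four arm-by-time cells and leaves out the control arm at day 84.

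The arms use different collection systems: the app for the intervention arm and Qualtrics for the control arm. A block left out of the control form would therefore not be exposed by a questionnaire shared between arms. If the omission reached the live form, it would remove the comparator at the endpoint. A day-84 assessment that was never offered cannot be collected once its window has passed.

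**Working it through.** **1. Is the blank real, or a column shift from text extraction?** The tick positions in the AUDIT row were compared with those of neighbouring rows in Table 1. I = intervention, C = control.

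| Row | Day 0 | Day 28 | Day 56 | Day 84 | Ticks |
|---|---|---|---|---|---|
| ITQ-PTSD | I, C | I, C | I, C | I, C | 8 |
| Readiness-to-Change Ruler | I, C | I, C | I, C | I, C | 8 |
| EQ-5D-5L | I, C | I, C | I, C | I, C | 8 |
| Timeline Follow Back (primary outcome) | I, C | I, C | I, C | I, C | 8 |
| Self-Efficacy Ruler | I, C | I, C | I, C | I only | 7 |
| AUDIT | I, C | I, C | I, C | I only | 7 |

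The ITQ-PTSD, Timeline Follow Back, AUDIT and Self-Efficacy rows were also split cell by cell. Each has 36 cells. Counting from zero, the first two have ticks in cells 2, 4, 21, 24, 26, 29, 31 and 34. The AUDIT and Self-Efficacy rows match them up to cell 31, and cell 34 (day 84, control) is present but empty. Nothing has shifted. PHQ-2, GAD-2 and the usability questionnaire also keep their day-84 control tick.

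**2. What does the outcome need?** Write I and C for the arm means and the subscript for the day. The between-arm difference in change is

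(I₈₄ − I₀) − (C₈₄ − C₀).

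Table 1 supplies I₈₄, I₀ and C₀ but not C₈₄. With the table as printed, the latest contrast that can be formed from observed data is

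(I₅₆ − I₀) − (C₅₆ − C₀),

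which is not the defined endpoint. A day-84 control value could only be extrapolated from days 0, 28 and 56.

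**3. How many values are at stake?** The inputs come from Sample Size Calculation: 74 per arm, a difference of 3 units, SD 5.6, correlation 0.7, 40% attrition, α 5% (taken as two-sided), power 80%.

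The plan's own figure reproduces if the variance is that of the mean of three follow-ups:

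- Unadjusted, single follow-up: 2 × [5.6 × (1.960 + 0.842) / 3]² = 54.7 per arm.
- Factor for the mean of three follow-ups: (1 + 2 × 0.7) / 3 = 0.8, so 54.7 × 0.8 = 43.8, rounded up to 44 per arm.
- Attrition: 44 / 0.6 = 73.3, rounded up to 74 per arm, or 148 in total. This matches the stated number.

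Expected control-arm AUDIT values at day 84:

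- as Outcome Measures describes: 74 × (1 − 0.40) = 44.4, about 44;
- as Table 1 is printed: 0.

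The sample size rests on the primary outcome, whose row is complete, so it does not change.

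**The case against.** The strongest reply is that this is a clerical slip with no consequence. Two places in the text, the Abstract and Outcome Measures, say that AUDIT is compared between the arms at day 84. The Control Arm section adds that controls complete every questionnaire, with no exception for day 84. Against these stands one blank cell.

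Table 1 also departs from the text elsewhere. It ticks the qualitative interviews for both arms, although the Qualitative Interviews section draws only on the intervention arm. It ticks the usability questionnaire at days 28, 56 and 84, although the Usability section gives day 28. The adjacent Self-Efficacy row has the same blank, which looks like a slip in preparing the table. A tick lost in text extraction is less likely, because the cell structure is intact, but it cannot be fully excluded.

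Most of this stands, and it sets the limits of the point. A reader might infer that the secondary outcome cannot be computed, or that all 74 controls will lack it. The documents do not support that. It would follow only if the table overrode the text, and the text states the opposite intention. Nor do the documents say that the Qualtrics form is built from Table 1. That is an inference from the table being named as the schedule, and the questionnaire set itself is in an appendix not shown here.

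The reply does not remove the contradiction. The Control Arm statement has controls complete questionnaires when they fall due, and the only place that sets due dates by instrument and arm is Table 1. This is also not detail that an article leaves to a fuller document: the article prints both the schedule and the outcome definition, and they disagree.

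**Conclusion.** The point holds as an internal contradiction. Table 1 schedules no control-arm AUDIT at day 84, while the Abstract and Outcome Measures define the only secondary outcome as the between-arm change in AUDIT from day 0 to day 84. An omitted tick is the likelier cause.

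The loss is conditional. If the control form follows the table, there would be no control-arm AUDIT scores at day 84 instead of about 44, and day 56 would be the last between-arm comparison. If the form follows the text, nothing is lost and only the table is wrong. The figure of 44 assumes 74 controls and that the planned 40% attrition applies equally to the control arm and to AUDIT.

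The correction is still needed, because the schedule is operative text and the potential loss could not be repaired afterwards. The Self-Efficacy Ruler has the same blank, but no named outcome depends on it.

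**What to change.** 1. Add the day-84 control tick to the AUDIT row of Table 1, so that the schedule agrees with the Abstract and Outcome Measures.
2. Confirm that the day-84 control form in Qualtrics contains AUDIT, before any participant reaches day 84.
3. Check whether the day-84 control blank in the Self-Efficacy Ruler row is intended. This is a matter of tidiness, not a condition for the secondary outcome.

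The cost is one corrected table cell, one check of an existing form and, if AUDIT proves to be absent, one added questionnaire block. Sample size and primary analysis do not change.

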#### Usability

We will examine the usability of the DrinksRation and BeAlcoholSmart platforms using the mHealth App Usability Questionnaire [37] at day 28. Questionnaire responses will be aggregated into (1) overall usability, (2) ease of use, (3) interface and satisfaction, and (4) usefulness. The results will be summarized with means and SDs.

### Qualitative Interviews

A random sample of 10 participants from the intervention arm will be invited to participate in a debrief session with the research assistant (RA; researcher GW) at the end of the intervention period. The 60-minute interview will address the participants’ experiences of using the DrinksRation app, their views on its acceptability and usability, and what further modifications could be made to improve their experiences of using the app. Interviews will be conducted on the web (via Microsoft Teams or Zoom [Zoom Video Communications, Inc]), and transcripts will be generated and used for analysis. A thematic analysis approach will be used. The findings from the qualitative interviews will be reported separately from the main trial results. Any participant who completes the day 84 outcome measure will receive a US $13 (£10 GBP) Love2Shop voucher as a gesture of goodwill.

### Adverse Events

It is not expected that participation in this study will lead to an increase in alcohol consumption or any untoward or unintended consequence. In this study, we have defined 4 categories of risk events (Textbox 3).

Adverse events and serious adverse events will be monitored throughout the intervention period via (1) direct contact between participants to the research team; and (2) a questionnaire presented to participants via the app on days 28, 54, and 84 after randomization. All reported events will be reviewed by a clinician (researcher DM), who, where required, will contact participants to perform a clinical interview and risk assessment. If concerns remain, a signposting booklet to relevant charities will be provided to the participants. The study RA will remove potentially unblinding information before sending it to the study clinician. The study clinician or the RA may register an adverse event based on the definitions outlined in Textbox 3.

Categories of risk events.

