**Adverse reaction**
Any untoward and unintended medical occurrence in a trial participant that is related to the intervention (eg, reaction to a questionnaire).

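### The unblinded research assistant may register events under definitions that turn on relatedness, and nothing says the blinded clinician's review settles the category

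*Protocol article*

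**What the plan says.** Four parts of the protocol article bear on this.

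- **Who is unblinded.** Randomization and Blinding lists three researchers, by initials, who know the allocation. Two of them "will be unblinded to treatment allocation to enable the management of the BeAlcoholSmart and DrinksRation platforms", and for recruitment and retention; the third prepares the statistical reports. For everyone else: "All other members of the study team will be blinded to treatment allocation".
- **Who the RA is.** Qualitative Interviews describes a "debrief session with the research assistant" and gives the RA's initials. They match one of the two platform managers. The study clinician's initials are not on the unblinded list.
- **How events are handled.** Adverse Events says that a clinician reviews all reported events and contacts the participant for an interview and risk assessment where required. It adds: "The study RA will remove potentially unblinding information before sending it to the study clinician". The next sentence reads: "The study clinician or the RA may register an adverse event based on the definitions outlined in Textbox 3".
- **What the definitions require.** Textbox 3 defines an adverse event without requiring a causal link. It defines an adverse reaction as "Any untoward and unintended medical occurrence in a trial participant that is related to the intervention (eg, reaction to a questionnaire"). The unexpected and serious categories build on these two.

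**The concern.** Two adjacent sentences in Adverse Events work against each other. The first spends effort on keeping the clinician from learning the arm. The second lets a person who knows the arm apply the same definitions. For any event whose category rests on the RA's entry, the redaction has protected nothing.

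The decision most exposed is relatedness. Someone who knows that a woman uses DrinksRation may be readier, or less ready, to call a complaint an adverse reaction than someone who does not know. The bias could run either way. What is at stake is the comparison between arms of adverse reactions with other adverse events, which is the trial's stated scheme for attributing untoward events to the intervention.

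There is a second, smaller risk. Information is removed if it is potentially unblinding, and no further rule is given. Where a participant blames a feature that only one arm has, deleting that detail could also take away what the clinician needs to judge relatedness.

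**Working it through.** No arithmetic applies. The check is a cross-reading of the sections.

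1. **RA's blinding status.** The initials in Qualitative Interviews match those of a researcher listed as unblinded in Randomization and Blinding. The RA is unblinded.
2. **Clinician's blinding status.** The clinician is not among the three listed researchers and so falls under "All other members of the study team will be blinded to treatment allocation". The redaction step makes sense only on that footing.
3. **Does registering involve classification?** Registration is to follow Textbox 3, which the article introduces as four categories of risk event:
   - adverse event: no causal judgement needed;
   - adverse reaction: related to the intervention;
   - unexpected adverse reaction: a subset of the previous category;
   - serious forms: may be a serious event or a serious reaction, so the same distinction carries over.

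   Applying these definitions therefore means choosing between related and not related for everything beyond the plain adverse event.
4. **Does the clinician's review settle the category?** The text says that all events are reviewed and that the clinician or the RA may register. It does not say that the review confirms, replaces or overrides an RA registration, and it names nobody as responsible for relatedness.
5. **Would later oversight reveal a difference by arm?** Under Project Management Group, that group sees blinded totals pooled across arms, so it could not. Under Executive Steering Committee, the committee receives reports from the unblinded statistician and from the RA. That might show counts by arm, but only after the categories have been assigned.
6. **When could redaction affect relatedness?** The Study Design overview says that the control lacks a drinks diary, interactive feedback and goal setting. The messaging section limits control notifications to email. A report naming one of the app-only features identifies the arm and falls under the redaction rule. This reaches app-specific reports only, and it is an inference: the article does not say that the event description or its circumstances are deleted.

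**The case against.** The strongest reply is that safeguards exist. Every reported event reaches the clinician, who can also interview the participant. The registering sentence speaks of an adverse event, which needs no causal judgement, and no section gives the RA the final word. A full protocol or safety procedure, not shown, may name who decides.

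Much of this stands, and it rules out several stronger readings that a reader might infer.

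- *That the RA classifies alone.* Not supported, because the clinician reviews all reported events.
- *That relatedness cannot be judged after redaction.* Not supported. The extent of redaction is not stated, the clinician may interview the participant, and a report can be reworded neutrally because both arms use a digital platform with reminders and questionnaires. The interview is held only where required, and it could itself reveal the arm.
- *That this split is the trial's only measure of harm.* Not so. Table 1 has alcohol consumption, PHQ-2, GAD-2, ITQ-PTSD and EQ-5D-5L collected in both arms during follow-up. Increased drinking would show in the primary outcome.
- *That questionnaire-related reactions could form a category comparable between arms.* Not so. Table 1 gives PHQ-2 and GAD-2 at days 7, 14, 21 and 28 in the intervention arm only, so exposure differs.
- *That the clinician should see the full text to judge relatedness.* This would recreate the bias at issue. It would also conflict with the blinding rule and unblind the person who writes the blinded report for the project management group.

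The reply does not remove the core. The article does more than leave a detail open: it states that the RA may register events under Textbox 3, which contains categories that depend on relatedness, and it does not subordinate that entry to the blinded review.

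**Conclusion.** The point holds in a limited form. As written, an unblinded person may apply definitions that turn on relatedness, next to a step designed to keep that judgement blind, and the blinded clinician's review is not said to prevail. Counts of adverse events against adverse reactions are therefore open to bias from knowledge of the arm. The article does not show that such bias would occur, or in which direction.

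The size cannot be calculated, since no expected number of events is given. The point is minor: adverse events are neither the primary nor the secondary outcome, and self-reported consumption does not pass through this process. The conclusion rests on two readings: that matching initials identify the same person, and that registering under Textbox 3 includes choosing among its categories. If a fuller safety procedure already gives the blinded clinician the final decision, only the wording of the article needs to be brought into line.

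**What to change.** In Adverse Events, replace the sentence on registration with wording to this effect:

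- The RA logs and forwards every report but assigns no Textbox 3 category.
- The blinded clinician assigns category, seriousness and relatedness for every event, and that entry is the one analysed.
- When redacting, the RA replaces arm-identifying feature names with neutral wording, such as a message from the study platform, and keeps the circumstances and timing of the event so that relatedness can still be judged.

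The cost is a few sentences and slightly more work for the clinician, who already reviews all reported events. No change to the blinding rule or to Textbox 3 is needed.
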